## Abstract

**Background:**

The aim of RApid community Point-of-care Testing fOR COVID-19 (RAPTOR-C19) is to assess the diagnostic accuracy of multiple current and emerging point-of-care tests (POCTs) for active and past SARS-CoV2 infection in the community setting. RAPTOR-C19 will provide the community testbed to the COVID-19 National DiagnOstic Research and Evaluation Platform (CONDOR).

**Methods:**

RAPTOR-C19 incorporates a series of prospective observational parallel diagnostic accuracy studies of SARS-CoV2 POCTs against laboratory and composite reference standards in patients with suspected current or past SARS-CoV2 infection attending community settings. Adults and children with suspected current SARS-CoV2 infection who are having an oropharyngeal/nasopharyngeal (OP/NP) swab for laboratory SARS-CoV2 reverse transcriptase Digital/Real-Time Polymerase Chain Reaction (d/rRT-PCR) as part of clinical care or community-based testing will be invited to participate. Adults (*≥* 16 years) with suspected past symptomatic infection will also be recruited. Asymptomatic individuals will not be eligible. At the baseline visit, all participants will be asked to submit samples for at least one candidate point-of-care test (POCT) being evaluated (index test/s) as well as an OP/NP swab for laboratory SARS-CoV2 RT-PCR performed by Public Health England (PHE) (reference standard for current infection). Adults will also be asked for a blood sample for laboratory SARS-CoV-2 antibody testing by PHE (reference standard for past infection), where feasible adults will be invited to attend a second visit at 28 days for repeat antibody testing. Additional study data (e.g. demographics, symptoms, observations, household contacts) will be captured electronically. Sensitivity, specificity, positive, and negative predictive values for each POCT will be calculated with exact 95% confidence intervals when compared to the reference standard. POCTs will also be compared to composite reference standards constructed using paired antibody test results, patient reported outcomes, linked electronic health records for outcomes related to COVID-19 such as hospitalisation or death, and other test results.

**Discussion:**

High-performing POCTs for community use could be transformational. Real-time results could lead to personal and public health impacts such as reducing onward household transmission of SARS-CoV2 infection, improving surveillance of health and social care staff, contributing to accurate prevalence estimates, and understanding of SARS-CoV2 transmission dynamics in the population. In contrast, poorly performing POCTs could have negative effects, so it is necessary to undertake community-based diagnostic accuracy evaluations before rolling these out.

**Trial registration:**

ISRCTN, ISRCTN14226970

**Supplementary Information:**

The online version contains supplementary material available at 10.1186/s41512-021-00093-8.

## Background

The world is in the midst of the SARS-CoV-2 (COVID-19) pandemic. Strict social distancing policies were introduced in many countries to suppress the first wave of infection with negative socio-economic consequences and widespread disruption to healthcare provisio n[1, 2]. Public health policy has focused on rapid identification and isolation (‘test and trace’ [3]) of new cases with targeted local responses to control resurgence of new infections, including areas previously deemed to be virus free [4]. However, efforts have been limited by both shortfalls in laboratory infrastructure, skilled human resources and testing reagents [5], delays in receiving results, and tracing subsequent contacts of positive cases [6]. Consequentially policy and guidance remain blunt, with delayed identification of localised outbreaks in the UK [7], sudden closure of travel corridors to Europe [8], and ongoing concerns about the feasibility of re-opening schools for the forthcoming academic year [9].

Point-of-care tests (POCTs) provide rapid results allowing people to receive immediate advice about self-isolation and treatment, reducing delays and costs associated with sample transportation and reliance upon specialised laboratories [10]. Additional public health impacts of rapid results include reducing residential transmission of infections and improving surveillance of health and social care staff. Whilst there has been accelerated development of POCTs for SARS-CoV-2, there is a lack of data on test safety, accuracy, and utility and performance [11]. Point-of-care antibody testing is well-established in other infections and is easily scalable [12], but initial studies in SARS-CoV-2 have had disappointing results [13]. Novel molecular technologies remain unproven in this context [14]. Accordingly, experts in diagnostics ward against widespread use of POCTs for SARS-CoV-2 before in-context evaluation [11, 15], and medical regulators require clear evidence of acceptable sensitivity and specificity prior to approval [16].

In-context evaluation must reflect both the dynamics of disease transmission and the capabilities of those performing the test to be confident about the test performance in a particular setting. Most of the current data for analytical performance of new POCTs for SARS-CoV-2 is from small and selective patient samples tested within laboratories by highly trained staff [17–19]. Studies in clinical settings have focused on hospitalised patients who are more likely to have higher viral loads, and may undergo invasive procedures to increase yield of respiratory tract sampling [20]. Community settings are characteristically different, and extrapolating results from elsewhere risks spectrum bias and low confidence in results [21]. POCTs must work well when there is a lower prevalence and severity of disease, overlap in presentation with other common clinical syndromes, and in elderly and frail patients who may mount weaker immune responses [22]. Community staff performing POCTs have little-or-no laboratory experience and no ready access to technical support. False negatives are more damaging as ambulatory patients can potentially propel community transmission, whilst false positives in otherwise healthy individuals could hamper efforts to kickstart return to work and education [23].

We therefore aim to undertake context-specific evaluations of multiple POCTs, across a national network of community settings. Our platform design will allow for flexibility in which POCTs are evaluated, changes in Public Health England (PHE) choice of reference standard, and dynamics of local infection rates. RApid community Point-of-care Testing fOR COVID-19 (RAPTOR-C19) is the community testbed to the COVID-19 National DiagnOstic Research and Evaluation Platform (CONDOR) [24]. CONDOR co-ordinates evaluation of diagnostic performance of in vitro diagnostics, across laboratory, community, interface medicine, and secondary-care networks.

This document summarises the key points of the RAPTOR-C19 diagnostic study protocol.

## Methods

### Aim

To assess the diagnostic accuracy of multiple current and emerging POCTs for active or past SARS-CoV-2 infection in the community setting

### Target condition

Active or past COVID-19 (symptomatic disease)

### Primary objective

Assess the standard diagnostic accuracy of POCTs for active SARS-CoV-2 infection compared to the Public Health England (PHE) reference laboratory standard or equivalent

### Secondary objectives

Assess the standard diagnostic accuracy of POCTs for past SARS-CoV-2 infection compared to the PHE laboratory reference standardAssess the diagnostic accuracy of POCTs for active SARS-CoV-2 infection against an enhanced composite reference standard using multiple tests data, linked electronic health records (EHR) data, and patient reported outcomes dataAssess the diagnostic accuracy of POCTs for past SARS-CoV-2 infection against an enhanced composite reference standard using multiple tests data, linked EHRs, and patient reported outcomes data

### Study design

RAPTOR-C19 will incorporate a series of prospective observational parallel diagnostic accuracy studies of SARS-CoV-2 POCTs against laboratory and composite reference standards in patients with suspected current or past COVID-19 attending community settings such as general practice. Because the current reference tests are imperfect, the RAPTOR-C19 protocol allows ‘standard’ and ‘enhanced’ diagnostic accuracy studies for active and past infection. As the study is observational in nature, point-of-care test (POCT) results will not be shared with the participant or used to make any clinical decisions.

### Participant selection

Both adults and children will be eligible for participation in the study. The inclusion criteria, listed in Table 1, are broad and designed to capture all-comers to general practice [25]. The clinical presentation of COVID-19 is heterogenous and still being characterised [26]. There are no reliable symptoms to discriminate severity of disease [27]. Restricting testing to a narrow spectrum of clinical features would therefore be inappropriate.

**Table 1 Tab1:** Inclusion and exclusion criteria

**Inclusion criteria** 1. Adults (> 16 years) (a) Male or female (b) With suspected current or past COVID-19 (symptomatic SARS-CoV2 infection) (c) Having OP/NP swab for laboratory SARS-CoV2 RT-PCR as part of clinical care/testing (d) Willing and able to give informed consent for participation in the study 2. Children (< 16 years old) (a) Male or female (b) With suspected current or past COVID-19 (symptomatic SARS-CoV2 infection) (c) Having OP/NP swab for laboratory SARS-CoV2 RT-PCR as part of clinical care/testing (d) Parent or legal guardian is willing and able to give informed consent for participation in the study **Exclusion criteria** 1. The participant may not enter the study if any of the following apply: (a) Adults unable to understand the study information and give consent to take part in the study (b) Need for immediate hospitalisation (c) Previously enrolled in this study in relation to the individual test being evaluated (d) Asymptomatic	

In general practice settings, the diagnosis of suspected current or past COVID-19 will be based on the clinical judgement of the primary care practitioner and/or the account of the participant. In all community settings, the clinical characteristics of the participant and reasons for testing will be documented.

The working definition of suspected current or past COVID-19 will be based on national advisory guidance [28, 29] to consider SARS-CoV-2 infection in people who, during the current pandemic, have the following:
Symptoms thought to be associated with COVID-19, including but not limited to: fever, cough, fatigue, dyspnoea, sputum production, anosmia, change in sense of taste, shortness of breath, myalgia, chills, dizziness, headache, sore throat, hoarseness, nausea, vomiting, diarrhoea, nasal congestionAcute respiratory distress syndromeEither clinical or radiological evidence of pneumoniaAtypical presentations, for example an acute functional decline or frailty syndrome in an older person, if they are immunocompromisedSymptoms and lived or worked in close contact with somebody who has tested positive for SARS-CoV-2, including NHS staff

### Setting

RAPTOR-C19 sites will be community based. The primary community setting will be primary care, focussing on general practices reviewing patients with suspected COVID-19 or acting as COVID-19 hubs. Practices that have submitted an expression of interest to take part in the study will be selected with the help of the National Institute for Health Research (NIHR) Clinical Research Network (CRN). RAPTOR-C19 sites will be reimbursed per patient recruited for their participation in the research. Participants will not be paid for their participation in the research.

Practices will be initially recruited through Oxford Royal College of General Practitioners (RCGP) Clinical Informatics Digital Hub (ORCHID) [30]. The surveillance platform of ORCHID is called the Oxford-RCGP Research and Surveillance Centre (RSC). General practices within this network are experienced in taking virology samples and serology specimens and have adapted their long established influenza surveillance to provide a sentinel system for COVID-19, including sero-surveillance [31]. Additionally, they have also previously successfully integrated POCTs into primary care clinical workflow in the 2018/2019 flu season [32, 33] with an additional pilot conducted across the 2019/2020 season. Recruiting patients into RAPTOR-C19 is an integral part of the planned 2020/21 ORCHID/PHE surveillance [34]. Patients who volunteer to provide samples for surveillance will have the opportunity to take part in RAPTOR-C19 in participating practices, and samples taken, with consent through RAPTOR-C19, will also be available to use for national surveillance.

### Eligibility assessment and recruitment

There are two routes to potential participants assessed for eligibility: opportunistic and remote.

Opportunistic recruitment is the primary recruitment strategy. This follows a patient-initiated contact with the RAPTOR-C19 study site, with symptoms consistent with current COVID-19 or past symptoms of possible/confirmed COVID-19.

Remote assessment represents a potential secondary recruitment strategy to be used if the primary recruitment strategy is not effective. The electronic health record (EHR) will be searched to identify people who have presented with symptoms of possible COVID-19, have had a confirmed diagnosis, or are a symptomatic household contact of a confirmed case. These people could then be invited for assessment of eligibility.

Asymptomatic individuals are not eligible.

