### Index tests and reference standards

#### Index tests (POCTs)

Biological samples to test for current SARS-CoV-2 infection will be collected from all participants. The index test will be at least one, but the intention is to assess multiple, candidate POCTs for active infection (all participants) or past infection (adults only). If multiple POCTs are being assessed, these may target a combination of current SARS-CoV-2 infection and past SARS-CoV-2 infection.

Participants will be asked to submit samples as appropriate for each candidate POCT by following the training and instructions provided by the manufacturer. These may include oropharyngeal/nasopharyngeal (OP/NP) swab, saliva, or blood from a finger prick. POCTs requiring finger prick blood samples will only be offered to participants > 10 years old. For POCTs that require assistance to complete, the researcher will assist the participant whilst adhering to safe PPE use. Where a participant completes the tests themselves, they will be observed by the researcher to monitor correct POCT use and ease of use and to identify sample quality issues.

The order in which the tests are conducted will not be randomised but the sequencing of the tests will be documented in the eCRF. Who performs the test, either participant or researcher, will also be recorded.

All POCT consumables will be discarded as clinical waste as soon as the POCT is complete and the results have been captured. No POCT samples will be retained by the RAPTOR-C19 team.

Both the researcher and the participant will be blinded from results of the reference test, as results will not be returned for at least 24 h after the POCT is taken. For paired index tests blinding will not be possible in a clinical environment. For qualitative index tests, we will capture a photograph of the result, for adjudication by independent research staff, blinded to any other clinical information or test results. POCT results will not be shared with the patient and they must not be used to make any clinical decisions.

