### Data sources

Table 3 outlines which data sources used to address each research question.

**Table 3 Tab3:** Data sources for analysis

Question	Data source					
	eCRF	*POCT index test* for *active* COVID-19	*Laboratory reference test* for *active* COVID-19	*POCT index test* for *past* COVID-19	*Laboratory reference test* for *past* COVID-19	*Composite reference standard*
*Standard* diagnostic accuracy of *active* infection	Yes	Yes—visit 1. Current and past suspects	Yes—visit 1. Current and past suspects	No	No	No
*Enhanced* diagnostic accuracy of *active* infection	Yes	Yes—visit 1. Current and past suspects	Yes—visit 1. Current and past suspects	No	Yes—visit 2. Current and past suspects	Yes
*Standard* diagnostic accuracy of *past* infection	Yes	No	No	Yes—visit 1. Current and past suspects	Yes—visit 1. Current and past suspects	No
*Enhanced* diagnostic accuracy of *past* infection	Yes	Yes—visit 1. Current and past suspects	Yes—visit 1. Current and past suspects	Yes—visit 1. Current and past suspects	Yes—visit 1 and 2. Current and past suspects	Yes

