### Summary statistics of diagnostic accuracy

Sensitivity, specificity, and positive and negative predictive values for each POCT will be calculated with exact 95% confidence intervals.

For the primary outcome and first secondary outcome:

For consecutive POCTs for active infection, the diagnostic accuracy of each POCT will be summarised independently using 2 × 2 tables for POCT (+/-) and the current standard PHE reference test (+/-) for active infection. For consecutive POCTs for past infection, the diagnostic accuracy of each POCT will be summarised independently using 2 × 2 tables for POCT (+/-) and the current standard PHE reference test (+/-) for past infection. Measures of diagnostic accuracy will also be presented adjusted for imperfect reference standard bias, using the best available estimate of the accuracy of the PHE reference test.

For the second and third secondary outcomes:

For consecutive POCTs for active infection, the enhanced diagnostic accuracy of each POCT will be summarised independently using 2 × 2 tables for POCT (+/-) and the composite reference standards as outlined in Table 4 (+/-). For consecutive POCTs for past infection, the enhanced diagnostic accuracy of each POCT will be summarised independently using 2 × 2 tables for POCT (+/-) and the composite reference standards (+/-) for past infection.

Results for the primary outcome will be stratified by adults vs children, by age group (< 16, 16–40, 40–60, 60+ years), by gender, by ethnicity and by spectrum of disease (a combined measure of symptom severity and duration). A further subgroup analysis will test for differences in diagnostic performance by practice, and if any differences are detected, associations with practice size, location and model of care will be explored.

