### Strengths and limitations

The prevalence of SARS-CoV-2 in the tested population will be the primary determinant of the rate at which RAPTOR-C19 can evaluate the accuracy of each POCT. The UK had surpassed a peak of SARS-CoV-2 infections at the time this protocol was being prepared for publication, with national easing of lockdown underway. COVID-19 testing capacity in the NHS took time to develop, with initial testing mainly occurring in the hospital setting, later through local COVID-19 ‘hubs’ and then national testing centres. At the height of the first peak, the prevalence of infection was > 30% in those tested [38]. As testing increased outside of the hospital setting, the prevalence of SARS-CoV-2 infections fell, due to a combination of decreasing national SARS-CoV-2 infection prevalence and increased testing in a broader population [39]. Whilst we welcome this reduction in prevalence, it results in larger sample sizes for clinical research.

By recruiting symptomatic people who are clinically suspected to have SARS-CoV2 infection, RAPTOR-C19 will increase the likelihood of identifying positive cases in the community above the background prevalence. To maximise recruitment RAPTOR-C19 will recruit from a base of high-throughput practices, with large practice populations, and/or practices acting as COVID-19 hubs, with wide geographical spread throughout the UK, including urban centres with high population density. Additional practices will be asked to act as stand-by sites where evaluation may begin rapidly in response to local outbreaks of SARS-CoV-2. This combined approach is intended to increase the likelihood of capturing positive cases in symptomatic people above the background national prevalence of SARS-CoV-2. From a public health point of view, correctly ruling-in active SARS-CoV-2 is just as important as ruling it out. Therefore, we need POCTs that are both highly sensitive and highly specific. The CONDOR triage process aims to identify POCTs that align with the MHRA specification based on the available data from the manufacturer or independent analytical analyses. By starting with a rigorous selection process, we reduce the probability of evaluating poorly performing POCTs.

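### The primary active-infection table pools current suspects with past and already confirmed cases, so its accuracy estimates and predictive values depend on the recruited mix

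*Protocol article*

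**What the plan says.** All references are to the protocol article.

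- **Recruitment.** Under Eligibility assessment and recruitment, the opportunistic route takes people "with symptoms consistent with current COVID-19 or past symptoms of possible/confirmed COVID-19". The remote route is a fallback: "Remote assessment represents a potential secondary recruitment strategy to be used if the primary recruitment strategy is not effective". If it is used, "The electronic health record (EHR) will be searched to identify people who have presented with symptoms of possible COVID-19, have had a confirmed diagnosis", and those found may be invited for eligibility assessment.
- **Eligibility.** Table 1 admits both current and past suspects. It requires symptoms and an RT-PCR swab taken as part of care or testing. It has no exclusion for a previous positive result.
- **Analysis population.** In Table 3, the row for standard accuracy for active infection, which is the primary objective, reads "Yes—visit 1. Current and past suspects" for both the POCT and the laboratory test. Baseline assessments says that adults suspected of current or of past disease share one visit schedule but are analysed differently.
- **Outputs.** "Sensitivity, specificity, and positive and negative predictive values for each POCT will be calculated with exact 95% confidence intervals". The primary outcome is stratified by age, gender, ethnicity and a combined severity and duration measure, with a further subgroup analysis by practice.
- **Prevalence.** Strengths and limitations describes high-throughput practices, hubs and outbreak stand-by sites, and adds: "This combined approach is intended to increase the likelihood of capturing positive cases in symptomatic people above the background national prevalence of SARS-CoV-2".

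**The concern.** A POCT for active infection is meant to be used in someone who is ill now and has no result yet. Someone who is past the illness, or already confirmed, differs in stage of infection and in what is known about them. Table 3 nevertheless places both kinds of participant in one primary 2x2 table, and nothing stated separates them by suspected status, prior diagnosis or recruitment route.

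A past or known case who is still RT-PCR positive counts towards sensitivity. One who is now RT-PCR negative counts towards specificity, where a positive POCT is scored as a false positive. The headline figures, which are to be judged against minimum values of 80% sensitivity and 95% specificity, would then partly reflect recruitment rather than the test. PPV and NPV carry a second dependence, on sample prevalence, which the plan means to raise above the national background.

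**Working it through.** **1. The plan's own figures.** Table 5 follows N = Se(1 − Se) / SE² / prevalence. For 90% sensitivity, 30% prevalence and SE 2.5%: 0.9 × 0.1 / 0.025² / 0.30 = 144 / 0.30 = 480, as stated; all 48 cells reproduce. The futility figures follow limit / (prevalence × (1 − Se)), for example 7 / (0.05 × 0.5) = 280, as stated. No sample size is disputed here.

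**2. Predictive values.** The inputs come from the protocol: a 90%/99% test at 30% or 5% prevalence (Stopping criteria) and minimum values of 80%/95% (Number of participants).

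PPV = Se·p / [Se·p + (1 − Sp)(1 − p)]; NPV = Sp(1 − p) / [Sp(1 − p) + (1 − Se)p].

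| Se / Sp | Prevalence | PPV | NPV |
|---|---|---|---|
| 90% / 99% | 30% | 0.270 / (0.270 + 0.007) = 97.5% | 0.693 / (0.693 + 0.030) = 95.9% |
| 90% / 99% | 5% | 0.045 / (0.045 + 0.0095) = 82.6% | 0.9405 / (0.9405 + 0.005) = 99.5% |
| 80% / 95% | 30% | 0.240 / (0.240 + 0.035) = 87.3% | 0.665 / (0.665 + 0.060) = 91.7% |
| 80% / 95% | 5% | 0.040 / (0.040 + 0.0475) = 45.7% | 0.9025 / (0.9025 + 0.010) = 98.9% |

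The test is the same within each pair; only prevalence changes.

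**3. Mixing in known cases.** The protocol gives none of the inputs needed, so these are assumptions. Let f be the share of the sample already confirmed, r the proportion of them still RT-PCR positive, and p = 5% the prevalence in the rest.

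- Share of reference positives who are known cases = f·r / [f·r + (1 − f)p].
- Observed sensitivity = (1 − share) × 90% + share × sensitivity in known cases.

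| f | r | Sample prevalence | Known share of reference positives | Observed sensitivity if 60% / 70% / 95% in known cases |
|---|---|---|---|---|
| 5% | 20% | 0.010 + 0.0475 = 5.8% | 17% | 84.8% / 86.5% / 90.9% |
| 10% | 50% | 0.050 + 0.045 = 9.5% | 53% | 74.2% / 79.5% / 92.6% |
| 20% | 80% | 0.160 + 0.040 = 20% | 80% | 66.0% / 74.0% / 94.0% |

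The protocol's two stopping scenarios each imply 60 reference positives (200 × 0.30 and 1200 × 0.05) and a limit of seven false negatives. Per 60 reference positives, the middle row gives about 60 × 0.258 = 15 false negatives at 60%, 60 × 0.205 = 12 at 70%, and 60 × 0.074 = 4 at 95%. A 90% test in ordinary presenters alone would give 6.

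**4. Direction.** The effect on sensitivity runs either way in the table. Prevalence can also move either way: with f = 10% and nobody still RT-PCR positive, it falls to 0.90 × 0.05 = 4.5%.

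**The case against.** The strongest reply is that much of this is intended or already mitigated, and several parts of that reply stand.

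- **Setting.** A reader might infer that hubs, outbreak sites and the record search together create an artificial case mix. The text does not support that. Symptomatic patients at practices and hubs are the intended population, and the enrichment passage does not list the record search. Hub recruitment mainly shifts prevalence, and in-sample PPV and NPV are standard cohort output.
- **The record search may never happen.** It is a fallback, and invitees must still be symptomatic and be having a swab. That limits numbers. It does not close the opportunistic route, which also admits confirmed past illness, or change Table 3.
- **Downward bias.** A reader might infer that sensitivity will be pulled down towards the 80% minimum. That needs assumed shares and an assumed low sensitivity in known cases; the same arithmetic gives an upward shift at 95%.
- **Blinding.** A reader might infer that a known earlier positive defeats the blinding. The plan says "Both the researcher and the participant will be blinded from results of the reference test, as results will not be returned for at least 24" hours, which concerns the study swab and is correct for it. Photographs of qualitative results are adjudicated by independent staff blinded to other information. An earlier known positive lies outside the 24-hour argument, but the point does not depend on this.
- **Stratification.** Severity and duration will capture part of the difference in stage. The headline table stays pooled, and prior diagnosis, suspected status and route are not identified.
- **The SAP is not shown.** It may add detail, but Table 3 states the primary analysis population outright, so this is not an omission left for the SAP to fill.

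**Conclusion.** The concern holds in a limited form. The protocol puts current and past suspects, including people already confirmed, into the primary active-infection table, while stating elsewhere that the two groups are analysed differently. Pooled accuracy for an active-infection POCT therefore depends on the recruited mix, in a direction that cannot be stated in advance.

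The predictive-value figures rest only on the protocol's own test performance and prevalence scenarios. They show how far PPV can move, not that the sample will sit at 30% while use sits at 5%. The sensitivity figures are illustrations on assumed inputs. Across the mixes shown, a 90% sensitivity in ordinary presenters appears as anything from 66% to 94%. The first evaluations run without stopping criteria, so any effect on early stopping would come later. The change is worth making because it is cheap and settles whom the primary estimate describes.

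**What to change.** 1. At baseline, record the recruitment route and any prior positive SARS-CoV-2 test with its date.
2. In Table 3 and under Summary statistics of diagnostic accuracy, make the headline active-infection table current suspects without a known positive test for the present illness episode. Report past suspects and previously confirmed cases as a separate stratum, and the pooled table as a secondary result. Tie the rule to the present episode: excluding anyone with any earlier positive would also remove people with an old infection and new symptoms, and could itself distort the spectrum.
3. Reconcile Table 3 with the statement in Baseline assessments that the two groups are analysed differently.
4. Report PPV and NPV from each POCT's sensitivity and specificity at fixed prevalences, using the 5% to 40% grid of Table 5. Label the in-sample values as specific to the recruited mix.

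The cost is a few baseline data fields and some wording. The headline table will hold somewhat fewer reference positives, and PPV will look less favourable at low prevalence.
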